## Abstract

**Background:**

Obesity is a serious public health issue affecting children in a progressively alarming manner; thus, nutrition education and behavior change interventions during childhood are a priority. Eating and physical activity behaviors are mainly influenced by the environment; therefore, lifestyle changes are often successful when interventions are implemented in places such as the home and school. Schools are fundamental for ensuring the development of students’ personalities, skills, abilities, and long-term behaviors.

**Objective:**

This study aims to measure the effect of an intervention designed for low-income Mexican schoolchildren, focused on promoting healthy lifestyles for the prevention of obesity and cardiometabolic diseases.

**Methods:**

The study design is a randomized clinical trial (NCT05945862), with intervention groups paired with control groups of the same grade. Four elementary schools were selected based on district socioeconomic status. The study will be carried out for 1 year in four phases: (1) initial measurements, including anthropometry, blood pressure, psychosocial diagnosis, family medical history, and behavior variables, such as nutrition knowledge, dietary intake, sleep time and quality, and physical activity; (2) intervention implementation based on social cognitive theory, the behavior change wheel with the capability, opportunity, and motivation influencing behavior theoretical framework, and the transtheoretical theory, covering topics related to nutrition and healthy eating, child health, personal and sleep hygiene, physical activity, psychosocial well-being, and motivation; (3) postintervention measurements, including initial and behavioral measurements and intervention indicators; and (4) 6-month postintervention evaluation using the same initial and behavioral measures as in phase 1. Baseline differences by age, sex, socioeconomic status, and location will be analyzed using chi-square tests (qualitative variables) and analysis of covariance (quantitative variables). Multiple linear regression will test potential baseline associations between dependent variables (anthropometrics and blood pressure) and independent variables (diet, exercise, sleep time, family interaction, psychosocial well-being, and perception of childhood obesity). For comparing changes between the intervention and control groups at postintervention and at 6-month postintervention in anthropometrics, blood pressure, and behavioral variables, we will use multilevel mixed-effects regression models, given the hierarchical structure of participants nested within schools and the repeated measurements over time. SPSS and STATA software will be used with a significance level of *P*<.05.

**Results:**

From October 2023 to August 2024, a total of 451 participants were recruited from 4 different elementary schools in Sonora, México. As of February 2026, the data collected are in the process of being captured and analyzed.

**Conclusions:**

The protocol is a comprehensive program designed for schoolchildren in Mexico, intended to be an effective strategy for promoting healthy lifestyles and preventing cardiometabolic diseases. It is important to continuously adapt the intervention before implementation and to evaluate it to ensure its sustainability and expand its impact on other elementary schools, improving the health and well-being of schoolchildren.

## Introduction

Childhood obesity is a critical public health issue that has substantially increased worldwide [1,2]. Obesity is associated with metabolic and cardiovascular risks at all ages, but it is particularly risky at ages 2 to 19 years due to early complications [2,3]. According to UNICEF (United Nations International Children's Emergency Fund), at least 1 in 20 children under 5 years old has obesity; the prevalence in children over 5 years and adolescents increases to 1 in 3 [4]. Mexico ranks first in childhood obesity in the world, with 37.3% of schoolchildren and 41.1% of adolescents with overweight and obesity [5]. Lifestyle is a crucial risk factor for obesity; among obesogenic environments are unhealthy diets high in saturated fat, simple carbohydrates, and sugary drinks, as well as low physical activity (PA) with long periods of sitting [6,7]. Family factors, such as dysfunctional families and parents’ low educational levels, are also fundamental in childhood obesity. Lyons et al [8] reported that family discord influences children’s eating habits, with a higher risk of eating disorders later in life. Other studies indicated that mothers’ perceptions of the child’s body image are a risk factor for childhood obesity. Mothers of children with overweight or obesity tend to underestimate their children’s weight, representing a barrier to obesity diagnosis and treatment [9]. On the contrary, psychosocial well-being is a protective factor since it reduces emotional and behavioral disorders that could lead to obesity in children and adolescents [10].

Paradoxically, mild to moderate food insecurity and childhood malnutrition are also associated with a higher prevalence of obesity [11]. Low- and middle-income countries have the highest prevalence of malnutrition: undernutrition (11.5% growth retardation and 1.4% emaciation) and overweight (8.5%), placing Mexico in seventh place for child malnutrition in Latin America. Both obesity and malnutrition are risk factors for complications such as type 2 diabetes (T2D) and cardiovascular diseases, which in turn cause high mortality rates and decreased productive life [12]. Unfortunately, T2D in adolescence and childhood has increased, reaching a diagnostic prevalence between 0.68% and 1.2% [13]. Childhood obesity negatively affects cardiac and vascular structure and function; it triggers metabolic conditions such as insulin resistance, elevated serum uric acid, and metabolic syndrome, among others [14]. Estimates suggest that in the future, obesity-attributed coronary heart disease will increase by 5% to 16% [15].

Regarding lifestyle risk factors, studies have shown that 67.6% of schoolchildren and 46% of adolescents are sedentary, while 80.1% and 91.5% spend more than 2 hours in front of a screen. This leads to an increase in BMI and, therefore, a decrease in cardiovascular health [16]. On the contrary, a healthy diet is one of the main protective factors. Each region has traditional diets that, generally, are healthy and promote biodiversity and food security with low environmental impact. The traditional Mexican diet (TMexD) is a healthy and sustainable diet that promotes dietary diversity and encourages the consumption of local foods [17]. The TMexD includes plant foods such as fruits, vegetables, and whole grains, as well as animal-based foods, which provide fiber, vitamins, minerals, antioxidants, protein, and healthy fats. Promoting TMexD among Mexican schoolchildren, especially at ages 6 to 12 years, is crucial because they are more selective and demanding when it comes to consuming food [18]. Regarding PA in childhood, recommendations include at least 60 minutes per day in addition to limiting screen time to 2 hours per day or less [19]. Therefore, it is essential to implement behavior-change interventions promoting healthy diets and PA for childhood obesity prevention [20].

Multiple studies have concluded that it is easier to prevent obesity at early stages of life than in adulthood [18]. These interventions must take into account lifestyle settings and conditions such as those found in schools, homes, families, etc [21,22]. Proposals should focus on generating changes in eating habits, increasing PA, and raising awareness about the importance of healthy lifestyles among children and adolescents [15,23]. With a comprehensive intervention and its evaluation in low-income communities, the most unprotected social sectors will be prioritized [24].

Home and school are the most influential places for children. The school is considered a suitable and safe environment for programs promoting healthy lifestyles [25]. Studies have reported that school interventions focused on reducing obesity are successful because schoolchildren are at an age where healthy habits can be instilled and maintained in the long term [26,27]. On the other hand, parents as providers also influence nutrition during school years since children usually consume what is available at home. Furthermore, researchers focus on schools as a fundamental component to ensure the development of students’ personalities and habits, as well as to promote their multiple intelligences, skills, abilities, and behaviors. From this age forward, the educational center is a privileged environment to achieve a balance of these pillars that will last throughout life [28]. Thus, it is a priority for schools to promote healthy habits [21].

Globally, there are successful programs promoting healthy habits. The Diabetes Prevention Program is one of the first T2D preventive programs that has been adapted for use in school settings [29,30]. In Mexico, programs such as “Specific Action Program 2007-2012 School and Health,” “National Strategy for the Prevention and Control of Overweight, Obesity, and Diabetes,” and others have been developed for obesity and T2D prevention and have been taken as a basis for interventions in some Mexican elementary schools [31-33].

The present intervention protocol addresses childhood obesity in an integrative and unconventional manner, generating multifactorial knowledge about family behavior, individual factors, and the school environment. The aim of this protocol is to measure the effect of an intervention designed for low-income Mexican schoolchildren, focused on promoting healthy lifestyles for the prevention of obesity and cardiometabolic diseases. Specific aim 1 is to analyze whether baseline anthropometric and behavioral variables are associated with psychosocial well-being, family interaction or functionality, and perceptions of childhood obesity in the home environment. Specific aim 2 is to evaluate the effectiveness of the intervention in terms of retention, motivation to change, fidelity, and acceptability of the program by schoolchildren. Specific aim 3 focuses on evaluating changes in health behaviors at the end of the intervention and after 6 months in knowledge, diet quality, exercise time, and sleep time and quality.

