### Behavioral Indicators (Before and After the Intervention)

#### 24-Hour Recall

Food intake will be assessed preintervention and postintervention in children in grades 4 to 6 using 2 nonconsecutive 24-hour recalls (24h-R), with the United States Department of Agriculture Automated Multiple-Pass Method [59]. The procedure consists of conducting an individual interview by a dietitian staff member and recording, on paper, the participant’s total food consumption during the day prior to the interview (from the time the individual woke up until the time they went to bed), ensuring that all foods and beverages are included. During the interview, key questions will be asked to stimulate the participants’ memory. To estimate the participant’s daily nutrient intake, recalls will be processed on the ASA24 site by the dietitian staff member, and for dishes not listed on the ASA24 platform, the ingredients will be individually itemized and recorded on the website.

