### Physical Activity

The 3-day physical activity recall assesses the time spent on different types of activities rated as light, moderate, intense, or very intense, recorded in periods of 30 minutes from when the interviewee got up in the morning until they went to sleep. Activities are assigned a metabolic equivalent of task (MET) level (moderate-to-vigorous physical activity ≥3 METs; vigorous physical activity ≥6 METs), and the summary scores are tallied as total METs per day [63]. This questionnaire has been validated in Latin American children and adolescents [64] and will be administered to participants from grades 4 to 6 [65].

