### Statistical Analysis

The normal distribution of the data will be verified using skewness, kurtosis, and Kolmogorov-Smirnov tests. Quantitative data with nonnormal distribution will be mathematically transformed for parametric analysis, or alternatively, nonparametric analysis will be used. Means and SDs will be calculated for continuous variables and percentages for categorical variables. To test age, sex, socioeconomic status, and location baseline differences, we will use chi-square tests for qualitative demographic variables (eg, socioeconomic level, family medical history, sport practice, etc) and analysis of covariance for quantitative variables (eg, anthropometrics, dietary intakes, HEI, TMexD, sleep time, BIP, family interaction, and psychosocial well-being). To evaluate specific aim 1, potential baseline associations of dependent variables (eg, anthropometrics and blood pressure) with independent behavioral variables (eg, dietary intakes, exercise and sleep time, family interaction, psychosocial well-being, and perception of childhood obesity) will be tested using multiple linear regression, starting with univariate regression (*P*<.2 and biological plausibility). Models will be built by a combination of univariate analysis and forward stepwise model selection using *P*≤.05 and biological plausibility. Preliminary models will be assessed for possible interactions (*P*≤.1) between sex and other variables included in the model, for collinearity (variance inflation factor<10), and for linear regression assumptions (linearity, normality, and homoscedasticity) using residual plots. Specific aim 2 will use mixed methods (qualitative and quantitative) to analyze results in terms of retention, fidelity, and acceptability of the intervention by children and school administrators. Specific aim 3 will compare the changes between the experimental arms (intervention vs control) from baseline to postintervention and to the 6-month follow-up in anthropometrics, blood pressure, HEI, dietary intakes, PA, sleep time, and knowledge. Primary analyses will follow the intention-to-treat principle. Given the hierarchical structure of the data (students nested within classrooms and classrooms within schools) and the repeated measurements over time (baseline, postintervention, and 6-month follow-up), intervention effects will be evaluated using multilevel mixed-effects regression models. Due to the cluster-based allocation, the intraclass correlation will be considered, potential attrition will be monitored, and all analyses will account for clustering to provide valid inferences. Models will include fixed effects for study arm, time, and the arm×time interaction, and random effects for classroom and school to account for intracluster correlation. Baseline values of the outcomes and covariates will be included as appropriate. Effect estimates with 95% CIs will be reported. We will examine model assumptions and fit indices. SPSS (IBM SPSS Statistics version 21.0) and STATA (StataCorp version 14.0) software will be used, with a *P* value <.05 for all statistical analyses.

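### The aim 1 model covers only the anthropometric part of the aim: behaviours are entered as predictors, so their association with family and psychosocial factors is not tested

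*Protocol article*

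**What the plan says.** The Introduction sets specific aim 1: to "analyze whether baseline anthropometric and behavioral variables are associated with psychosocial well-being, family interaction or functionality", and with perceptions of childhood obesity in the home. Anthropometric and behavioural variables stand on one side of the question; psychosocial, family and perception variables stand on the other.

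Statistical Analysis, naming the same aim, describes "potential baseline associations of dependent variables (eg, anthropometrics and blood pressure) with independent behavioral variables". The predictor list runs "dietary intakes, exercise and sleep time, family interaction, psychosocial well-being, and perception of childhood obesity) will be tested using multiple linear regression". The Abstract (Methods) gives the same division without an 'eg': "dependent variables (anthropometrics and blood pressure) and independent variables (diet, exercise, sleep time, family interaction, psychosocial well-being, and perception of childhood obesity".

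On model building, Statistical Analysis starts from univariate regressions at P<.2 and continues: "Models will be built by a combination of univariate analysis and forward stepwise model selection using" P≤.05. Biological plausibility is attached to both thresholds. No variable is named as kept regardless of its P value.

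On who has data, 24-Hour Recall states "Food intake will be assessed preintervention and postintervention in children in grades 4 to 6", and Physical Activity says of its questionnaire that it "will be administered to participants from grades 4 to 6". Participants enrols lower (up to grade 3) and upper (grades 4 to 6) school groups. Table 3 gives the total as 173 + 117 + 86 + 75 = 451.

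**The concern.** A regression estimates how its outcome relates to its predictors. It has no coefficient for how two predictors relate to each other. With diet, exercise and sleep on the same side as family interaction, psychosocial well-being and perception, the behavioural half of aim 1 has no estimate.

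That half matters to the article's own rationale: the Introduction reports that family discord influences children's eating habits, and that children eat what is available at home.

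Two features of the model also weaken the half that is covered. Data-driven selection can remove the factors the aim asks about, or keep them only net of behaviours, and P values reported after selection are too small because they ignore the search that produced the model. Models with recall-based diet or activity terms can describe only grades 4 to 6 under complete-case analysis, and Statistical Analysis does not say so where it describes aim 1.

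**Working it through.** **Is the behavioural half estimated anywhere?** The article states no sample size or power for aim 1, so there is no figure to reproduce. Each described baseline analysis was compared with the aim.

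| Analysis | Outcome side | Predictor side | Behaviour versus family or psychosocial factors? |
|---|---|---|---|
| Aim 1 regression (Abstract; Statistical Analysis) | Anthropometrics, blood pressure | Diet, exercise, sleep, family interaction, psychosocial well-being, perception | No |
| Baseline analysis of covariance (Statistical Analysis) | Includes dietary intakes, HEI, sleep time, family interaction, psychosocial well-being | Age, sex, socioeconomic status, location | No |
| Diet indicators at baseline (Indicators of Diet Quality) | Cardiometabolic risk factors | Diet quality | No |

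**How many children remain?** The share in grades 4 to 6 is not given; 40% to 60% is assumed.

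- 0.40 × 451 = 180; 0.60 × 451 = 271; midpoint 226.
- Standard errors grow by √(451/271) = 1.29 to √(451/180) = 1.58, with √(451/226) = 1.41 at the midpoint.

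**How often would one factor miss P≤.05?** The true partial correlation r is assumed. By the Fisher z approximation, m = atanh(r) × √(n − 3), and the chance of missing is 1 − [Φ(m − 1.96) + Φ(−m − 1.96)]. For r = 0.10 and n = 451: m = 0.1003 × √448 = 2.12, so the chance of reaching P≤.05 is 0.565 and of missing it 0.435. Clustering is ignored.

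| n | r = 0.10 | r = 0.15 |
|---|---|---|
| 451 | 43% | 11% |
| 271 | 62% | 30% |
| 226 | 68% | 38% |
| 180 | 73% | 48% |

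**What if a family factor acts only through behaviours?** A simulation of 400 runs per sample size applied the P<.2 screen and then forward selection at P≤.05, without a plausibility rule. The assumptions were: the family factor correlates 0.4 with each of three behaviours; each behaviour has coefficient 0.2 on the outcome; residual SD 1; two unrelated candidates. The outcome variance is 1 + 0.04 × (3 + 6 × 0.16) = 1.158, so the factor's total correlation with the outcome is 0.2 × 3 × 0.4 / √1.158 = 0.22. The factor was absent from the final model in 85% of runs at n = 451 and 87% at n = 226. This is an extreme case (full mediation). It shows that a clear marginal association can vanish from the reported model even at full sample size.

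**The case against.** The strongest reply is that aim 1 is largely addressed. Anthropometrics are outcomes, the family, psychosocial and perception variables are named predictors, and each starts in a univariate regression. This stands: a reader might infer that aim 1 is not tested at all, and the article does not support that. The 'eg' before the outcomes leaves some room, but the article labels the behaviours as independent variables, and the Abstract repeats the division without 'eg'. The gap in the behavioural half remains.

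A reader might also infer that the anthropometric results are biased. The documents do not support that. The aim asks about association, and an association adjusted for behaviours is legitimate. It answers a narrower question, and the report must say which one is meant.

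On selection, biological plausibility is part of the rule and might be used to keep a factor. Deletion is therefore a risk, not a certainty. But plausibility is joined to the P threshold by 'and', so as written it adds a condition instead of protecting a variable. That a real factor would usually be dropped cannot be claimed in general: at r = 0.15 the miss rate is 38% at n = 226 and stays below half across the assumed range.

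On grades, the restriction is disclosed in the measurement sections. It affects only complete-case models holding recall-based diet or activity terms. Family adherence to the traditional diet and sleep carry no stated grade limit, and models without recall terms can keep all grades. The article does not state how missing predictors are handled in aim 1.

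**Conclusion.** The point holds in this form. The described analysis covers the anthropometric part of aim 1 and leaves the association of behaviours with psychosocial well-being, family interaction and perception untested. This follows from the text and needs no assumption.

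The other two parts are conditional. Selection may drop the aim's factors or keep them only net of behaviours. Complete-case models with recall terms would rest on about 180 to 271 of 451 children, with the chance of missing P≤.05 rising from about 43% to 62–73% (r = 0.10) or from about 11% to 30–48% (r = 0.15). Those figures depend on the assumed 40–60% grade share and the assumed correlations.

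The consequence is limited to a baseline, cross-sectional aim. A reader might extend it to the randomised comparison, but aim 3 uses separate mixed-effects models and is unaffected. The change should be made because it lets the trial answer a question it sets itself.

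**What to change.** - Add aim 1 models with diet quality and activity as dependent variables, both labelled grades 4 to 6, and with sleep as a dependent variable.
- Keep psychosocial well-being, family interaction and perception, with age, sex and school, in every aim 1 model, without stepwise deletion.
- For anthropometry and blood pressure, report a full-sample model without recall-based diet and activity terms, then a second model labelled grades 4 to 6 that adds them.
- State the grades and the number of children analysed for each model.
- Label the added models as specified after data collection, since Table 3 already ticks data analysis for two of the four schools.

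The cost is revised analysis text and a few more regressions on data already captured. The downside is more coefficients to report, including null ones.

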## Methods

### Ethical Considerations

The protocol was approved by the Institutional Research Ethics Committee from the Technological Institute of Sonora (approval letter number 249). All procedures will be in accordance with the ethical standards of the ethics committee and with the Declaration of Helsinki. Prior to the study, written informed consent will be obtained from both the school principals and one parent or tutor, and informed assent will be obtained from the participants to authorize participation and the use of photographs and images. The intervention will be explained in detail, and participants will be informed that they are free to withdraw at any time, personal information will be kept confidential, and results will be presented after the complete intervention. The protocol was registered on ClinicalTrials.gov [34] with the identification number Protocol Record NCT05945862 (data registration: July 10, 2023), Healthy Lifestyle Promotion Program in Communities from the Yaqui Valley. Participants will be coded with a 3-digit number to keep their data confidential, and privacy will not be infringed. Identifying details will be omitted for the data analysis and publication processes.

